## Methods

### Study design

This will be a delayed intervention RCT, with all participants ultimately receiving the periodontal intervention benefits (Fig. 1).

**Fig. 1 Fig1:**
[figure not shown]
Study plan schema

### Ethical approval

The study was approved by the University of Adelaide Human Research Ethics Committee and the Central Australian Human Research Ethics Committee. Written informed consent will be obtained from study participants before their involvement in the trial.

### Inclusion criteria

Aboriginal people aged 18+ years who have lived in the study location for 2+ years, and who plan to live at their current location for the next 2 years, with CKD (i. on dialysis; ii. eGFR levels of <60 mls/min/1.73 m^2^ (CKD Stages 3 to 5); iii. ACR ≥30 mg/mmol irrespective of eGFR (CKD Stages 1 and 2); iv. diabetes plus albuminuria (ACR ≥ 3 mg/mmol) irrespective of eGFR), with at least 12 teeth at baseline and having moderate or severe periodontal disease will be invited to take part in the study. Periodontal disease will be assessed using the US Centers for Disease Control and Prevention and the American Academy of Periodontology definitions, whereby a case of moderate periodontitis is considered as the presence of either two sites between adjacent teeth with 4 mm + attachment loss or at least two such sites with 5 mm + pockets, and severe periodontitis as having at least two sites between adjacent teeth with 6 mm + attachment loss and at least one 5 mm + pocket [44].

### Randomisation

Randomisation will be developed by biostatisticians at the Australian Research Centre for Population Oral Health using a random number generator. Randomly selected block sizes of 4, 6 and 8 will be used. This will guarantee an equal number of participants in each intervention arm within the blocks, with any differences in confounders and other characteristics being then due to chance. Randomisation will be done using field staff laptop computers. The field staff will be required to register the participants in the trial prior to identifying the randomised group. These data will be unable to be altered, thus allowing the randomisation process to be audited.

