### Data analysis

Data analysis will use intention-to-treat and per-protocol approaches, with the effect on primary outcomes based on intention-to-treat analyses. Analyses will follow a general course of descriptive statistics such as distributions and measures of association. Simple cross-tabulations and more elaborate repeated-measures analyses will follow. In brief, the plan for the analysis of each aim is:*Aim 1: Extent and severity of periodontal disease compared with national-level counterparts:* Extent of periodontal disease will be defined by the number of periodontal sites in the mouth with a given pocket depth (PD) divided by the number of teeth in the mouth x 100. The National Survey of Adult Oral Health dataset will enable comparison with both general and Aboriginal population-level estimates [49]. General analysis will comprise Chi-square and Student’s t-test within the study sample and non-overlapping 95 % confidence intervals when comparing with population estimates.*Aim 2: Changes in cIMT, measures of renal function and CKD/CVD-related death:* The primary analysis will compare changes in cIMT and 95 % confidence intervals. Secondary analyses will examine each outcome variable using separate mixed models, to allow inclusion of all participants without having to impute data. We will use generalised linear mixed models for non-continuous outcomes. Models will include treatment group as a fixed effect. Analyses will be conducted to identify subgroups that modify the response to the intervention (eg. active/passive smoking, socio-economic status). Model assumptions will be checked and appropriate adjustments made. We will conduct sensitivity analyses to assess uncertainty in key parameters. Death and cardiovascular events, both binary outcomes, will be analysed using the chi-square test with frequencies and percentages per treatment arm and odds-ratios or other measures of treatment effect reported along with summary measures. The Greenhouse-Geisser correction for the F-test will be used to adjust the degrees of freedom for deviation from sphericity. Logarithmic transformation of the data will be performed where appropriate. A post hoc correlation analysis by the Spearman rank-correlation method will be performed to evaluate the relationship between the changes in renal function and cIMT from baseline to 6, 12 and 24 months following periodontal therapy. The same will also be done for measures of periodontal health and cIMT. Effect sizes will be calculated by dividing the mean of change scores by the pooled estimate of the standard deviation. Effect measures will also be presented through calculation of number-needed-to-treat and its associated 95 % confidence interval. The statistically significant level will be at α < 0.05.

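### Entry runs from dialysis to early CKD, but allocation is not stratified by dialysis status and deaths and CV events are compared by a plain chi-square test: valid, but a cheap gain in precision and balance is given up

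*Protocol article*

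**What the plan says.** **Who enters.** The Inclusion criteria (Protocol article, Methods) admit people "with CKD (i. on dialysis; ii. eGFR levels of <60 mls/min/1.73 m^2^ (CKD Stages 3 to 5"), people with macroalbuminuria "irrespective of eGFR (CKD Stages 1 and 2"), and people with "diabetes plus albuminuria" at any eGFR. One trial therefore spans dialysis patients and people with preserved filtration.

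**What the article says about kidney status.** The Background section on measuring CKD treats low eGFR and proteinuria each as a separate predictor of cardiovascular illness and death and of progression to ESKD.

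**How they are allocated.** The Randomisation section states: "Randomly selected block sizes of 4, 6 and 8 will be used". It covers the generator, release of the allocation by laptop after registration, and audit. It names no stratification factor and describes the result as arms of equal size within blocks, "with any differences in confounders and other characteristics being then due to chance".

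**How they are analysed.** The Data analysis section (Aim 2) names no covariate for the primary comparison of cIMT change. Of the mixed models it says: "Models will include treatment group as a fixed effect". Death and cardiovascular events are assigned a chi-square test, with odds ratios or other effect measures. No dialysis or CKD-stage term appears anywhere in the section.

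**The concern.** Dialysis status is an eligibility item, so it is known for every participant before allocation. On the article's own account, kidney status predicts the outcomes being compared. Permuted blocks fix the total number in each arm but do nothing to even out the number of dialysis patients. A chi-square test of deaths or events then makes no use of a known predictor, and it cannot correct the estimate if one arm happens to hold more dialysis patients.

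Two things are at stake. One is precision in the death and cardiovascular-event comparisons. The other is interpretation: a visible imbalance in dialysis share would invite an argument after the fact about whether to adjust. Covariates can be settled later in an analysis plan. Stratified allocation cannot, because it must be in place before the first participant is randomised.

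**Working it through.** The article gives no figure for imbalance, so there is none to reproduce on this point. The one input taken from it is N = 600 randomised, 1:1 (Sample size; Randomisation). The dialysis share, the death rates and any difference in cIMT change between entry groups are not given. They are assumed below.

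**Step 1. Chance imbalance in dialysis share.** With equal arms and overall share p, the standard deviation of the between-arm difference is √(4p(1−p)/600), and the 95% range is ±1.96 times that. At p = 0.30: √(4 × 0.21/600) = 0.0374, so ±7.3 points. An exact hypergeometric calculation agrees:

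| Dialysis share (assumed) | 95% range, points | P(difference ≥ 5 points) | P(difference ≥ 10 points) |
|---|---|---|---|
| 10% | ±4.8 | 0.04 | 0.0001 |
| 20% | ±6.4 | 0.13 | 0.003 |
| 30% | ±7.3 | 0.18 | 0.010 |
| 40% | ±7.8 | 0.21 | 0.016 |
| 50% | ±8.0 | 0.22 | 0.018 |

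**Step 2. Effect on the death comparison.** Assume 24-month death rates of 20% on dialysis and 4% otherwise, a gap of 16 points. At a 30% share:

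- Overall rate: 0.3 × 0.20 + 0.7 × 0.04 = 0.088.
- Shift from an imbalance at the 95% limit: 0.073 × 0.16 = 0.012, or 1.2 points.
- Standard error of the unadjusted risk difference, 300 per arm: √(2 × 0.088 × 0.912/300) = 0.023, or 2.3 points. The shift is about half of this.

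Across the range of shares, with the same death rates:

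- 10% share: overall rate 0.1 × 0.20 + 0.9 × 0.04 = 0.056; shift 0.048 × 0.16 = 0.8 points; SE √(2 × 0.056 × 0.944/300) = 1.9 points.
- 50% share: overall rate 0.5 × 0.20 + 0.5 × 0.04 = 0.12; shift 0.080 × 0.16 = 1.3 points; SE √(2 × 0.12 × 0.88/300) = 2.7 points.

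The shift is proportional to the assumed gap: at a 30% share, each point of gap in death rate adds 0.073 points.

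**Step 3. Precision recovered by adjustment.** The share of outcome variance explained by dialysis status is p(1−p) × gap² / [rate × (1 − rate)].

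- 30% share: 0.21 × 0.16² / (0.088 × 0.912) = 0.067. The SE is multiplied by √(1 − 0.067) = 0.966, a cut of about 3%. That is worth about 7% more participants (1/0.933 = 1.07).
- 10% share: 0.09 × 0.16² / (0.056 × 0.944) = 0.044, a cut of about 2%.
- 50% share: 0.25 × 0.16² / (0.12 × 0.88) = 0.061, a cut of about 3%.

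**Step 4. Effect on the primary outcome.** Use the 472 evaluable participants and an assumed gap in cIMT change between dialysis and other entrants. The shift at the 95% limit of imbalance is gap × 1.96 × 2√(p(1−p)/472). For shares of 20% to 50%:

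- gap 0.03 mm: 0.002 to 0.003 mm
- gap 0.05 mm: 0.004 to 0.005 mm
- gap 0.09 mm: 0.007 to 0.008 mm

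The target difference is 0.026 mm. The last gap equals one full planning SD, so it is a deliberately large assumption. Adjusting for dialysis status would raise power at 236 per arm from 0.881 to 0.886–0.889, 0.896–0.904 and 0.928–0.952 respectively. The starting value is 0.881 rather than the article's 0.80 because its inputs (0.026 mm, SD 0.09, two-sided 0.05) need only 378 evaluable participants. That is a separate matter and does not affect this point.

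**The case against.** Unstratified permuted blocks are an ordinary, valid design at this size, and the remark in the Randomisation section that remaining differences are due to chance is correct. The unadjusted standard error already includes the variation that dialysis imbalance produces. An imbalance of 10 points or more is rare (at most 0.018 in Step 1), the matched example moves the death comparison by only half a standard error, and stable differences between entry groups largely cancel in cIMT change. All of this stands. It limits the point to a loss of efficiency.

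Several stronger readings are tempting, and the article does not support them.

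- *The models contain treatment alone.* The text says treatment group is included, not that nothing else is. A full covariate list may sit in an analysis plan that is not shown.
- *A dialysis subgroup is missing.* The article writes "Analyses will be conducted to identify subgroups that modify the response to the intervention (eg. active/passive smoking, socio-economic status"), which is a list of examples. Leaving dialysis out of it excludes nothing.
- *The comparison is biased.* A chance excess of dialysis patients moves one trial's estimate. Over repeated randomisations the estimate is centred correctly and the test keeps its level.
- *Dialysis is the strongest predictor of outcome.* This is plausible, but the article does not rank entry groups.
- *Stratifying by dialysis would even out those at risk of CKD progression.* It would do so only in part. Dialysis entrants have already met the renal-replacement component, but non-dialysis entrants with eGFR below 15 have already met the ESKD component, and the macroalbuminuria route has already met the albuminuria component. How that endpoint handles such entrants is a different question.

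The objection does not remove two stated choices: an allocation scheme described in detail without a stratum, and a chi-square test for deaths and events.

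**Conclusion.** The point holds as a cheap improvement to a valid design. For assumed dialysis shares of 10% to 50%, the plan leaves an avoidable 95% chance range of about ±4.8 to ±8.0 points in dialysis share. At a 30% share with death rates of 20% and 4%, the 95% limit of that imbalance moves the death comparison by about 1.2 points against a standard error of about 2.3, and adjustment recovers about 3% of the standard error. The effect on cIMT change is likely small, at 0.002 to 0.008 mm under the assumed gaps.

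These sizes rest on an assumed dialysis share, assumed death rates and assumed gaps in cIMT change. A smaller share or a narrower gap makes the point smaller. The structural part rests on the text alone: a mixed entry population, kidney status described as prognostic, no stratum, and a chi-square test with no stratification. A reader should not take this as evidence of bias or an inflated type I error, or conclude that adjustment has been ruled out.

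**What to change.** 1. **Allocation.** Prepare separate permuted-block lists for participants on dialysis and not on dialysis. Field staff already register each participant before the group is shown, so dialysis status can be entered and locked at that step.
2. **Models.** Include dialysis status as a fixed effect in the Aim 2 models. This should accompany stratified allocation, since a standard error that ignores the stratum would not reflect the balance gained.
3. **Deaths and cardiovascular events.** Replace the plain chi-square test with a comparison stratified by dialysis status, for example a Mantel-Haenszel test and risk difference. If an odds ratio is reported, state that it is conditional on dialysis status.

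If recruitment has begun, leave the allocation list as it is and apply only items 2 and 3, fixed before outcome data by arm are seen. That recovers most of the benefit.

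The cost is one extra registration field, one model term, and one more set of incomplete blocks at the end of recruitment. The sample size does not change.

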### Periodontal intervention

The periodontal intervention will be based on the technique described by Tonetti and colleagues [43]. This involves intensive removal of subgingival dental plaque biofilms by scaling, root-planing and removal of teeth that cannot be saved, following administration of local anaesthesia. The intervention will be performed by registered oral health professionals and will occur in three visits; baseline, 3 months and 6 months post-baseline.

### Location

The study will be undertaken in Alice Springs, Northern Territory of Australia.

### Engagement, recruitment and retention

This study will rely on commitment from the Alice Springs primary and tertiary health care sector. Conveniently, the Alice Springs Renal Dialysis Unit is located a few metres from the Alice Springs-based Northern Territory Oral Health Services. Specific recruitment strategies will include: establishing service agreements with the key Aboriginal community-controlled health and mainstream government health services in Alice Springs; liaising with community champions previously involved in Alice Springs-based research projects; engaging with key community stakeholder groups; encouraging word-of-mouth spread of knowledge about the study; advertisements in local newspapers and radio shows; flyers in post boxes in high-density Aboriginal locations and presentations made to community groups. A passive snowballing technique will also be employed, with participants asked to contact any Aboriginal friends, family and peers who may be interested in partaking. Retention strategies will involve: (1) employing staff who are committed to following up participants despite challenges in doing so; (2) ensuring participants are contacted on a regular basis to check accuracy of contact details; (3) maintaining relationships with appropriate stake holders; (4) ascertaining contact details of three key personnel who may know the whereabouts of participants should the study team be unable to contact them; (5) sending birthday and Christmas cards to participants; and (6) faciliating one-on-one relationships between study staff and participants, with study staff ideally seeing each of their participants for each phase of the research. We will allow 2 years for recruitment.

### Follow up

Participants will be followed for 24 months after randomisation. Because this is a pragmatic study evaluating the delivery of periodontal care, rather than therapeutic agents, an open design is necessary. Appropriate care will be taken to ensure standardised, and where feasible, blinded outcome evaluation—“PROBE” design [45]. During follow-up, all study participants will attend clinic visits at 6 months, 12 months and at 24 months.

### Sample size

Based on a recent study of Australian Aboriginal adults with periodontal disease, it was estimated that a sample size of 472 would be necessary to detect a difference in cIMT of 0.026 mm (SD 0.09) [46] at the significance criterion of 0.05 and a power of 0.80. Allowing for 20 % attrition, 592 participants would be necessary at baseline, rounded to 600 for convenience.

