**Methods:**

The study will be a randomised controlled trial. All participants will receive the periodontal intervention benefits, with the delayed intervention group receiving periodontal treatment 24 months following baseline. Inclusion criteria include being an Aboriginal Australian, having CKD (a. on dialysis; b. eGFR levels of <60 mls/min/1.73 m^2^ (CKD Stages 3 to 5); c. ACR ≥30 mg/mmol irrespective of eGFR (CKD Stages 1 and 2); d. diabetes plus albuminuria (ACR ≥ 3 mg/mmol) irrespective of eGFR), having moderate or severe periodontal disease, having at least 12 teeth, and living in Central Australia for the 2-year study duration. The intervention involves intensive removal of dental plaque biofilms by scaling, root-planing and removal of teeth that cannot be saved. The intervention will occur in three visits; baseline, 3-month and 6-month follow-up. The primary outcome will be changes in carotid intima-media thickness (cIMT). Secondary outcomes will include progression of CKD or death as a consequence of CKD/cardiovascular disease. Progression of CKD will be defined by time to the development of the first of: (1) new development of macroalbuminuria; (2) 30 % loss of baseline eGFR; (3) progression to end stage kidney disease defined by eGFR <15 mLs/min/1.73 m^2^; (4) progression to end stage kidney disease defined by commencement of renal replacement therapy. A sample size of 472 is necessary to detect a difference in cIMT of 0.026 mm (SD 0.09) at the significance criterion of 0.05 and a power of 0.80. Allowing for 20 % attrition, 592 participants are necessary at baseline, rounded to 600 for convenience.

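### The 472 given as the evaluable number for 80% power does not follow from the printed inputs, which need about 380; the 20% attrition allowance was probably applied twice

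*Protocol article*

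**What the plan says.** The Sample size section of the protocol article gives a complete set of inputs and a result: "it was estimated that a sample size of 472 would be necessary to detect a difference in cIMT of 0.026 mm (SD 0.09"). The significance level is set at 0.05 and the target power at 0.80. The attrition step follows: "Allowing for 20 % attrition, 592 participants would be necessary at baseline, rounded to 600 for convenience". So 472 is presented as the number needed before any allowance for loss.

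The Methods paragraph of the abstract carries the same claim: "A sample size of 472 is necessary to detect a difference in cIMT of 0.026 mm (SD 0.09"), followed by the same 592 and 600.

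Two further inputs are found elsewhere. The Randomisation section implies 1:1 allocation ("This will guarantee an equal number of participants in each intervention arm within the blocks"). The Data analysis section repeats the significance level without saying whether tests are one-sided or two-sided ("The statistically significant level will be at α < 0.05"). The Measures section defines the primary outcome as the change in cIMT over 24 months. The Sample size section does not say whether the SD of 0.09 is that of a change or of a single measurement.

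**The concern.** The four printed inputs fix the sample size for a comparison of two means, and 472 is not what they give. It is about a quarter too high for 80% power, yet it is very close to the number obtained once 20% attrition has been added. The plan then adds 20% attrition to it.

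This is the only power statement in the article, it concerns the primary outcome, and the abstract repeats it. A reader cannot tell from it how many evaluable participants the 80% target needs, what power the planned 600 provides, or how much loss to follow-up the design can absorb. On the printed inputs, one attrition allowance would call for about 475 randomised. The plan recruits about 125 more people with chronic kidney disease than that, and "592 participants would be necessary at baseline, rounded to 600 for convenience" explains only the last 8 of them.

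**Working it through.** **Inputs.** Difference 0.026 mm, SD 0.09, significance 0.05, power 0.80 and attrition 20% (Sample size). Allocation 1:1 (Randomisation). Two-sided testing is an assumption; the one-sided result is in step 2.

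**Step 1: the number from the printed inputs.** Normal formula, per arm:

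n = 2 × (1.960 + 0.842)² × (0.09/0.026)² = 188.1, so 189 per arm and 378 in total.

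The t-test version gives 189.06, so 190 per arm and 380 in total. The printed figure is 472, and 472/378 = 1.25.

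**Step 2: can an ordinary variant give 472?**

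| Variant (normal formula) | Total |
|---|---|
| One-sided 0.05, power 0.80 | 298 |
| Two-sided, power 0.85 | 432 |
| Two-sided, power 0.90 | 504 |
| 2:1 allocation | 426 |
| Alpha 0.025 | 456 |
| SD 0.095 and difference 0.0255 (least favourable rounding of both inputs) | about 436 |

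None gives 472.

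**Step 3: reproducing the plan's figures with attrition.**

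- One allowance: 189/0.80 = 236.25 per arm. Taken as 236, the total is 472, as printed.
- Two allowances: 189/(0.80 × 0.80) = 189/0.64 = 295.3 per arm. Rounded up to 296, the total is 592, as printed.
- The step as the article describes it: 472/0.80 = 590, not 592.

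A double allowance therefore yields both printed numbers, while the described route misses the second. The match needs 236.25 rounded down and 295.3 rounded up, so it is strong evidence but not proof.

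**Step 4: power on the printed inputs (two-sided 0.05).**

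| Evaluable | Normal formula | Noncentral t |
|---|---|---|
| 378 | 0.802 | 0.800 |
| 472 | 0.881 | 0.879 |
| 480 (600 less 20%) | 0.886 | 0.885 |
| 600 | 0.943 | 0.942 |

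**Step 5: what the planned 600 provides.**

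- Detectable difference at 80% power with 480 evaluable: 0.09 × 2.802 × √(4/480) = 0.023 mm.
- Attrition at which 80% power is just kept: 1 − 380/600 = 0.367, or 1 − 378/600 = 0.37; about 37%.

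**Step 6: the input that would make 472 correct.**

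- SD = √(236/2) × 0.026/2.802 = 0.101. This does not round to 0.09.
- Equivalently, 0.09 is a single-visit SD and the correlation between baseline and 24 months is about 0.375, since 0.09 × √(2 × (1 − 0.375)) = 0.101.
- With SD 0.101 and 480 evaluable, the standardised difference is 0.026/(0.101 × √(4/480)) = 2.82, and power is Φ(2.82 − 1.96) = 0.805.

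**The case against.** The strongest objection concerns cause. The article does not show its calculation, and nowhere says that 472 already includes an allowance. An SD of about 0.101 would also give 472, and that could come from treating 0.09 as a single-visit SD when the outcome is a change. If so, the number would be right and the printed input wrong. The attrition step should then stay, and the figures of 88% power and 37% tolerable attrition would not apply: with 480 evaluable, power would be about 80%. This objection stands. The double allowance is the likely explanation, not an established fact, and the correction must allow for both possibilities. It does not rescue the text, because under either explanation the printed inputs and the printed result disagree.

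The second objection is that nothing is endangered. That is largely right. On the printed inputs the trial is larger than 80% power requires, and the endpoint, the significance level and the analysis are untouched.

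A reader might also infer that a final evaluable number between 378 and 472 would be counted as a failed sample size. The documents do not support this. No section makes 472 a stopping, success or reporting threshold, the retention strategies carry no numerical target, and the Data analysis section does not use the figure.

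**Conclusion.** The point holds as a reporting error in the sample size statement. On the printed inputs, with two-sided testing and 1:1 allocation, 80% power needs about 380 evaluable participants. The stated 472 is about 25% above the normal-formula figure and corresponds to about 88% power. A double attrition allowance is the best-supported explanation, since it gives both 472 and 592, but it remains an inference.

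A reader might conclude that the trial is underpowered or lacks the stated 80% power. The documents do not support that: the error is conservative, and on the stated inputs 600 randomised with 20% loss exceeds the 80% target by about 8 percentage points. Nor do they show that enrolment should be cut, because a margin for an uncertain SD or for heavier loss could be a sound choice; the article simply does not present it as one.

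The figures rest on 0.09 being the SD of the change in cIMT, which the article does not confirm.

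**What to change.** Retrieve the original calculation, state whether the test is two-sided and say which SD 0.09 is. Then take one of two routes, in both the Sample size section and the abstract.

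- **If 0.09 is the SD of the change in cIMT:** state about 380 evaluable (190 per arm) for 80% power to detect 0.026 mm. Apply the 20% allowance once, giving 380/0.80 = 475 randomised (476 for equal arms). State that 600 randomised gives about 88% power after 20% attrition, and describe the margin above 476 as deliberate, with its reason.
- **If another input produced 472** (for example an SD of about 0.101): print that input, keep 472 as the evaluable number, and correct 592 to 590.

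The cost is a few sentences of wording. No change in enrolment is needed on either route.
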